## Abstract

**Background:**

Quality of residential care for people with severe dementia is in urgent need of improvement. One reason for this may be the assumption that people with severe dementia are unaware of what is happening to them. However, there is converging evidence to suggest that global assumptions of unawareness are inappropriate. This trial platform study aims to assist care staff in perceiving and responding to subtle signs of awareness and thus enhance their practice.

**Methods/Design:**

In Stage One, a measure of awareness in severe dementia will be developed. Two focus groups and an expert panel will contribute to item and scale development. In Stage Two observational data will be used to further develop the measure. Working in four care homes, we will recruit 40 individuals with severe dementia who have no, or very limited, verbal communication. Data on inter-rater reliability and frequency of all items and exploratory factor analysis will be used to identify items to be retained. Test-retest and inter-rater reliability for the new measure will be calculated. Correlations with scores for well-being and behaviour and with proxy ratings of quality of life will provide an indication of concurrent validity. In Stage Three the new measure will be used in a single blind cluster randomised trial. Eight care homes will participate, with 10 residents recruited in each giving a total sample of 80 people with severe dementia. Homes will be randomised to intervention or usual care conditions. In the intervention condition, staff will receive training in using the new measure and will undertake observations of designated residents. For residents with dementia, outcomes will be assessed in terms of change from baseline in scores for behaviour, well-being and quality of life. For care staff, outcomes will be assessed in terms of change from baseline in scores for attitudes, care practice, and well-being.

**Discussion:**

The results will inform the design of a larger-scale trial intended to provide definitive evidence about the benefits of increasing the sensitivity of care staff to signs of awareness in residents with severe dementia.

**Trial Registration:**

ISRCTN59507580 http://www.controlled-trials.com.

## Background

Quality of care for people with severe dementia in residential settings is poor and in urgent need of improvement [1]. This represents perhaps one of the major current challenges in dementia care [2]. In the UK, estimates of the number of people with dementia living in care homes range from a quarter of a million people to 368,400 [3,4], with two-thirds of these residents having a moderate to severe degree of dementia. In the US, half of all nursing home residents have moderate to severe dementia. The need for improvements in quality of care has been highlighted by the Department of Health's 'Dignity in Care' campaign and by the Joint Committee on Human Rights [5]. 'Dignity' is defined in this context as involving care that promotes the self-respect of the older person [6]; treating the person as an object rather than a person would be one example of the care practices this campaign is aiming to eradicate. Perhaps the greatest challenge for care homes is to uphold the dignity of people with severe dementia, who may need considerable help with basic functions, such as feeding, dressing, washing and toileting, and whose communication ability may be very limited. The current emphasis on dignity implies that the care of people who appear to lack self-awareness or awareness of their surroundings may be especially challenging for care staff. The presumed unawareness of the person with dementia may lead to marginalisation, where caregiving interactions become task-focused, pay limited attention to the person's reactions and fail to acknowledge the person's remaining ability to respond to stimulation. This study, funded by the Medical Research Council, will revisit and challenge these assumptions of unawareness, so as to provide a context for dignity in the care of people with severe dementia.

The capacity to show awareness can be defined as the ability to make an accurate appraisal or appropriate response in a given domain, for example in relation to internal states, external stimuli, symptoms, or changes in functioning. Awareness may be expressed at various levels, from basic perceptual and sensory awareness through to sophisticated self-awareness [7]. Individual variability in aspects of awareness and in relation to different domains has been documented in people with mild to moderate dementia, with studies focusing mainly on identification of deficits in awareness. Neuropsychological models have attempted to account for this variability in terms of changes in cognitive functioning [8] while others have pointed to the role of psychological factors in determining response to illness [9]. In recent comprehensive reviews we have drawn these perspectives together in a biopsychosocial framework [10,11].

Limited attention has been given to awareness and subjective experience in people with dementia living in residential care, who are likely to have moderate to severe levels of impairment. It has been suggested that awareness lessens as scores on cognitive tests decline [12], with the implication that at a certain stage of cognitive decline awareness is lost. However, correlational studies focusing mainly on the earlier stages of dementia suggest that the relationship between level of cognitive decline and degree of unawareness is not straightforward [13]. Therefore, some awareness about one's situation and functioning might be retained even in the presence of severe cognitive impairment [14]. Our comprehensive review of the literature reporting assessment of awareness in dementia [15] found only two small-scale studies focused on awareness in people with severe dementia. However, we have recently completed what we believe is the first systematic study of awareness in people with moderate to severe dementia [16]. This involved analysis of 304 interviews with 80 individuals with dementia residing in long-term care. MMSE scores ranged from 0-20 with a modal score of 0, indicative of severe cognitive impairment. All participants showed awareness in a range of domains, while about two-thirds also showed unawareness in at least one area. Our findings provided evidence that people with moderate to severe dementia are often aware to a considerable degree, and perhaps more than is often assumed by those most closely involved in providing care. Focus groups held with care staff suggested that where residents talk in ways that suggest an unrealistic appraisal of their situation or a confusion between past and present reality, they are likely to be regarded as globally 'unaware', negating the aspects of retained awareness that are also evident. While this study provided evidence about awareness in the context of retained capacity to communicate verbally, those for whom verbal communication was very limited or absent were not included.

For individuals who cannot communicate verbally, level of awareness can only be assessed through detailed observation of their behaviour and reactions. Here we can draw parallels with research on other groups where verbal communication is compromised. Following severe traumatic brain injury, demonstrable awareness is absent in coma and vegetative states, but people in minimally conscious states show subtle but definite behavioural indications of awareness with evidence of meaningful interaction with the environment [17]. The development of a comprehensive assessment measure based on detailed observation of behaviour, the Wessex Head Injury Matrix (WHIM) [18], has indicated that such patients often have a greater degree of awareness than previously assumed. The WHIM, which has good reliability and validity, has been found to be a more appropriate and sensitive measure than other tools currently used to assess emergence from coma and the minimally conscious state [19]. The WHIM has been used to demonstrate the effects of interventions such as postural change on levels of awareness and responsiveness for people in the minimally conscious state, supporting the view that some kinds of sensory stimulation may promote the expression of awareness [20].

In view of this, it is likely that people with severe dementia who do not communicate verbally may show awareness, at least at the sensory and perceptual level, and may express through their behaviour a response to environmental stimuli and interactions with caregivers. Consistent with this, studies have demonstrated preserved reactions to sensory stimuli in people with very severe dementia [21]. Observation of reactions and responses to particular stimuli will provide an indication of the person's awareness at any given time. If care staff can be trained to observe these behavioural indications of awareness, and understand them as such, this should help to increase their sensitivity to the needs of the person with severe dementia and to find ways of increasing awareness and responsiveness through, for example, sensory stimulation, postural change, or environmental adaptation, with benefits to residents in terms of quality of life and quality of care, and to staff in terms of increased job satisfaction and morale. Recent parallel accounts from a practitioner and a caregiver suggest that working in this way can increase sensitivity to responses and needs, and enrich the caregiving experience [22,23].

An approach of this kind requires the ability to influence the attitudes and practices of care staff. Training must be carefully designed to achieve the required outcomes. A systematic review of staff training in dementia care in nursing homes [24] identified 21 studies, mainly from the USA. Results in terms of outcomes for staff were generally positive, but outcomes for residents appeared to be better, and maintained longer, where the training involved a combination of initial information designed to enhance knowledge, attitudes and beliefs, environmental change to support the implementation of new skills, and the provision of cues or reminders to prompt and reinforce the use of new skills. Of particular relevance to the current proposal, providing care staff with 10 hours of training in being sensitive to non-verbal signals of emotion in people with severe dementia [25] resulted in significant increases in positive affect 6 weeks after the training for the residents in the intervention group, but this was not maintained over time. In our study we intend to address issues of maintenance by giving staff an instrument they can use routinely to assist them in focusing in detail on the person's level of awareness and emotional sensitivity. In summary, training needs to consist of more than just teaching sessions; our proposal is that by regular use of the instrument, staff will be able to operationalise indicators of awareness, and learn to apply them to the individual. This in turn will help staff to have more understanding of and empathy with residents with severe dementia; greater empathy and more positive attitudes are associated with reduced risk of staff burnout and increased job satisfaction [26].

In order to enable staff to undertake effective and systematic observation of behaviour, a reliable instrument for the assessment of awareness in severe dementia is required. This instrument should be simple to use and easy to integrate within the tasks of caregiving, and should provide clear operational definitions of the behaviours to be monitored. Existing measures do not meet this requirement. Dementia Care Mapping [27] has been useful in evaluating quality of care in residential settings, but focuses on more complex behaviours and requires an extensive time commitment from specially-trained and accredited raters. DCM lacks sufficient sensitivity to capture subtle aspects of behaviour in people with severe dementia [28]. Dementia Care Mapping (DCM) was designed as a standalone practice development tool, and was not intended for use as part of everyday practice. While it provides clear operational definitions of more complex behaviours, it was not designed to capture subtle aspects of behaviour in people with severe dementia. Other measures, such as the Positive Response Scale [28] or the Quality of Life in Late-Stage Dementia scale [29], rely to a considerable extent on interpretation of responses by the rater (for example, whether the residents shows 'enjoyment'), rather than recording discrete observable behaviours (for example, whether the resident tracks the carer with his/her eyes for at least 30 seconds). Fortunately, a valuable model is provided by the WHIM, described above, which offers a simple but reliable format for members of the multi-disciplinary team, as they go about their duties, to observe and record discrete behaviours exhibited by patients with severe brain injury. We propose to develop and validate a new measure for the assessment of awareness in people with severe dementia, based on the content and format of the WHIM. This will help staff to identify behavioural expressions of awareness in a way that can be readily integrated with on-going care provision. We will then conduct an initial intervention study in the form of a cluster randomised trial (CRT) in which we will train staff to use the measure with residents who have severe dementia, support them in adapting their practice to take account of their observations, and evaluate the impact on quality of care and on residents' quality of life. This will inform the design of a larger-scale trial, for which our core hypothesis is that training care staff to identify indications of awareness in people with severe dementia and enhance their care practice on the basis of their observations will result in improved quality of care and quality of life for the residents concerned.

## Design and Methods

This trial platform study will be conducted in three stages. First, we will explore the perspectives of paid and family carers, so as to incorporate their diverse experience and expertise, and with assistance from an expert panel we will prepare an initial draft of the proposed instrument. Second, we will conduct an observational study as a basis for further developing the new measure and evaluating its reliability and validity. Exploratory factor analysis will assist in refining the tool and hypothesising its factor structure. Third, we will conduct a randomized controlled trial (RCT) of an intervention in which staff are trained to use the new measure and outcomes are evaluated. Each stage is outlined in more detail below.

## Ethics and research governance

Establishing a sound ethical framework for this research is a key priority, as it involves observation of people with dementia, a vulnerable group who may not be able to give informed consent. The provisions of the Mental Capacity Act (2005) will be followed. In each case, the research will be explained to the potential participant in a conversational manner, at a time and in a place where the person is most likely to feel relaxed, with a supporter present where available. Consent will be sought where the person appears to understand and retain the information given, and makes a clear expression of their decision. Realistically, as the project will focus on people with severe dementia, we anticipate that most, if not all, participants will be unable to give informed consent. In each case where the person is unable to give informed consent, a suitable person will be approached to give an opinion on the person's likely views regarding participation. Wherever possible this will be a family member; where no family member is available, a suitable person will be asked to be the consultee, following appropriate guidance from the National Assembly for Wales. This research can only be effective if it includes people with severe dementia; the concern regarding dignity and human rights of such individuals in care settings makes this an important area to address, with the potential for benefits for this population. The research carries minimal risks for participants. All observational work will be undertaken in public areas of the homes, and on each occasion the researchers will explain the purpose of their presence in general terms to residents in the area. For individual assessments, the researchers will be trained to identify non-verbal indications that the person is unwilling to be involved in the research, and will not continue with any procedure which the person finds distressing. With regard to research governance, the project will be sponsored by Bangor University. A favourable ethical opinion has been granted by the relevant University ethics committee and by the North West Wales NHS Research Ethics Committee (reference 08/WNo01/60).

## User involvement

We will work closely with the User Carer Programme of NEURODEM Cymru (hosted by the Alzheimer's Society in Wales) to ensure that the perspectives of family carers and advocates for people with dementia contribute to the development of the project. A project steering group will be established and representatives from the group will meet regularly with the research team. Results will be disseminated to lay groups through links with the Alzheimer's Society, and through the Residents & Relatives Association.

## Stage One. Item and scale development

### Design

This is a qualitative study using focus group methods and an expert panel.

### Participants

Focus group participants will include managers, nurses, care staff and family caregivers recruited through participating care homes and local Alzheimer's Society branches.

### Procedure

Two focus groups will be conducted, one with formal carers including care home managers, nursing staff and care assistants (n = 10), and one involving family carers with relatives in care homes or in the community (n = 10). Participants will discuss their views on awareness, identify what they consider key indicators of awareness in people with severe dementia, and consider the relevance, appropriateness and applicability of the WHIM items and format. An expert panel consisting of psychometricians and practitioners and researchers in dementia care (n = 10), recruited through professional networks with which the applicants are associated (e.g. DeNDRoN), will convene to assimilate the findings of the focus groups, suggest item reduction and modification of the WHIM, and formulate an appropriate rating system.

### Analysis

Qualitative thematic and content analyses of transcripts of the focus group sessions will be conducted.

### Outputs

A preliminary version of the new measure will be prepared.

## Stage Two. Development of the awareness measure

### Design

Observational data will be used alongside ratings made by care staff and the research team in order to further develop the measure of awareness in people with severe dementia. Data will be subjected to exploratory factor analysis to further refine the tool for use in Stage Three.

### Participants

We will identify 4 care homes in North Wales, within which we will recruit 40 individuals with severe dementia who have no, or only very limited, verbal communication.

### Measures for assessment of the person with dementia

• Severity of dementia: Functional Assessment Staging (FAST) [30], a widely-used brief system for categorising severity of impairment in people with dementia. [In the initial funding application we proposed to use the Global Deterioration Scale [31], but following initial piloting we decided to replace it with the FAST which provides a more fine-grained classification.]

• Cognitive functioning: Guy's Advanced Dementia Schedule [32]; a structured assessment of cognitive ability that involves measuring responses to familiar objects. [In the initial funding application we proposed to use the Severe Impairment Battery [33], but as initial piloting indicated floor effects on this measure we replaced it with the GADS.]

• Behaviour: Behavioural Assessment Scale of Later Life (BASOLL) [34]; a reliable and valid rating of self-care ability, functioning and behaviour, completed by staff.

• Well-being: Positive Response Scale (PRS) [28]; an observational scale completed by a trained rater that focuses on the person's affective response to the environment.

• Quality of life: Quality of Life in Late-stage Dementia (QUAL-ID) [29]; an 11-item scale completed by a proxy with reference to the person's quality of life in the preceding week.

• Awareness: Wessex Head Injury Matrix (WHIM) [18,19]; an hierarchical list of 62 observable behaviours, ranging from 'looks at person briefly' to 'knows the name of one staff member'. This will be modified in line with recommendations from Stage One.

### Procedure

All participants will be observed for two 30-minute periods using the PRS and assessed with the GADS to provide a profile of their current level of well-being and cognitive functioning. A designated member of the care staff will be interviewed for each participant, and will provide background information, make ratings of severity of dementia (FAST) and behavior (BASOLL), and provide proxy ratings of quality of life (QUAL-ID). Where possible a family member will be interviewed to obtain background information and provide parallel proxy ratings of quality of life. Next, observational data using the modified WHIM will be collected for all participants. Observations of each participant will be carried out by a single rater in public areas of the care home, while participants are awake, over a period of 30 minutes on 5 different occasions and at different times of the day in order to capture any fluctuations in levels of awareness. A second independent rater will concurrently observe a sample of 12 residents (3 from each home) on all 5 occasions. Any further additional behaviours identified during the observations will be operationally defined by the research team in concise and concrete terms. Draft definitions will be tested prospectively with participants and further revised if necessary.

### Analysis

(a) Determining the content of the new measure: Test-retest reliability for *each individual item *will be calculated using data from all 40 participants relating to two assessment sessions, held at the same time of day, one week apart. Inter-rater reliability for *all items *will be assessed using data from the 12 participants who were observed concurrently by two independent raters. Behaviours that cannot be rated reliably will be excluded, as will any behaviours that occurred in fewer than 5% of assessments or were not observed at all. Systematic exploratory factor analysis (EFA) will be used to generate an hypothesised factor structure and to further modify the tool by excluding non-informative items. Sample size estimates for an EFA range from 5 to 20 or more subjects required per item, depending on the nature of the data. Five assessments with each of 40 participants will yield 200 uses of the tool. We acknowledge that a dependency structure might exist and will test for this, but it is unlikely to reduce the effective sample size below 100, which will be sufficient provided the emergent scale consists of no more than 20 items.

(b) Determining the properties of the new measure: Test-retest and inter-rater reliability for the new measure will be calculated on the same basis as for the constituent items. The relationship between awareness and cognitive impairment will be assessed in terms of correlations between scores on the new measure and scores on the GADS. Higher levels of observed awareness are predicted to be associated with greater well-being and higher proxy ratings of quality of life; therefore, correlational analysis will be used to identify the relationship between scores on the new measure and scores for well-being (PRS), behaviour (BASOLL), and quality of life (QUAL-ID proxy scores produced by staff and family carers), providing an indication of concurrent validity.

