### Outputs

The key output from this stage will be a reliable, valid and parsimonious measure of awareness in people with severe dementia that takes into account user perspectives, and which is presented in a format that can be easily used by care staff, accompanied by a comprehensive and accessible user manual.

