### Intervention

In the intervention condition, care staff will be introduced to the measure in teaching sessions, gain hands-on experience of using the measure under the guidance of a trainer, and then undertake observations of allocated residents and receive group supervision to support the development of care practice with those residents. An accredited trainer will advise on, and support the process of, staff training. For each home, the intervention period will last for 8 weeks. In weeks 1 - 2, two 90-minute training sessions will be provided, and each staff member involved will be given an individualised observation schedule. In weeks 3 - 8, each staff member will conduct six 10-minute observations per week and receive 30 minutes face-to-face or telephone contact with the researcher. Observations will be scheduled so that (a) pairs of staff members make independent observations of the same resident; (b) each staff member observes each identified resident on a number of occasions; (c) each staff member observes at least three different residents; and (d) each staff member observes at least two residents over an extended period of at least three weeks. Observations will be conducted in public areas of the home while the residents are awake. All staff will participate in fortnightly one-hour group supervision sessions, where they will be encouraged to consider variations in residents' level of awareness, and to identify and implement ways of supporting increased levels of awareness.

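### The new measure's Stage Two reliability is estimated on the same 40 and 12 residents used to choose its items, so it is biased upward by an unknown amount, and no estimate in new residents is planned

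*Protocol article*

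**What the plan says.** All references are to the Protocol article.

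- **Stage Two, Analysis (a), test-retest.** Item test-retest reliability "will be calculated using data from all 40 participants relating to two assessment sessions, held at the same time of day, one week apart".
- **Stage Two, Analysis (a), inter-rater.** Item inter-rater reliability "will be assessed using data from the 12 participants who were observed concurrently by two independent raters". The Procedure section gives the design: "A second independent rater will concurrently observe a sample of 12 residents (3 from each home) on all 5 occasions".
- **Stage Two, Analysis (a), item selection.** "Behaviours that cannot be rated reliably will be excluded, as will any behaviours that occurred in fewer than 5% of assessments". An exploratory factor analysis of the same observations then removes further items. No numerical reliability cut-off is stated.
- **Stage Two, Analysis (b).** "Test-retest and inter-rater reliability for the new measure will be calculated on the same basis as for the constituent items".
- **Stage Two, Outputs.** The product is described as "a reliable, valid and parsimonious measure of awareness in people with severe dementia".
- **Stage Three, Participants and Data analysis.** The eight homes are new. Of the four analysis purposes, the only one that tests the measure itself is a confirmatory factor analysis.
- **Stage Three, Intervention.** In the intervention homes the observation schedule is arranged so that "pairs of staff members make independent observations of the same resident". No reliability analysis is attached to these pairs.

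**The concern.** An item's observed reliability is its true reliability plus sampling error. Discarding items on the observed value tends to keep those whose error was favourable. If the scale built from the survivors is assessed on the same observations, that favourable error is counted again as reliability. In a new sample it would not recur.

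At stake is the evidence behind the word reliable in the Stage Two output. The measure is the core of the Stage Three intervention and is meant for everyday use by care staff. If the plan is followed as written, the only planned reliability coefficients are development-sample values that overstate what other residents would yield.

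**Working it through.** **1. Are the data the same?** The phrase about the same basis could mean only the same method. Under either reading the residents are the same: Stage Two recruits 40 in total, of whom 3 × 4 homes = 12 are double-rated, giving 12 × 5 = 60 paired observations. No hold-out sample, cross-validation or optimism correction is described. The prospective testing mentioned in the Stage Two Procedure concerns draft definitions of added behaviours and is not a second reliability sample.

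**2. Does a later stage supply a fresh estimate?** The Stage Three Data analysis section plans a test of factor structure in the new homes, which is not a reliability estimate. Stage Three Outputs promises more information on the measure without naming reliability.

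**3. Is there a stated figure to reproduce?** No reliability coefficient, cut-off or precision is given. The related counts do reproduce: 5 × 40 = 200 uses of the tool, and 100 ÷ 5 per item = 20 items.

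**4. Direction and size by simulation (600 replicates per setting).**

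Inputs from the article: 40 residents with two sessions; 12 residents × 5 occasions × 2 raters; a starting list of 62 behaviours before Stage One changes it; at most 20 items in the final scale.

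Assumed inputs, not in the article:
- 40 or 62 candidate items.
- Each binary item is scored 1 when a latent value exceeds its threshold. The latent value has a common trait with loading 0.5, a stable item-specific part (SD 0.6), a session part (SD 0.7) and a rater part (SD 0.45).
- Item reliabilities are either equal, or unequal through variation in the session and rater SDs.
- Kappa cut-offs for test-retest/inter-rater are 0.2/0.4 (lenient) or 0.4/0.6 (strict). Under the lenient rule an optional cap keeps the 20 items with the highest summed kappas.

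Formulas: item kappa = (p_o − p_e)/(1 − p_e). Total-score ICC for two ratings = (MSB − MSW)/(MSB + MSW). Bias = mean ICC on the selection data minus mean ICC of the same items on fresh data of the same size.

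Ranges over the four item pools (40 or 62 items, equal or unequal reliability):

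| Selection rule | Mean items kept | Test-retest ICC bias | Inter-rater ICC bias |
|---|---|---|---|
| None (control) | 40 to 62 | −0.003 to +0.001 | −0.004 to 0.000 |
| Lenient, no cap | 21.2 to 40.5 | +0.024 to +0.033 | +0.006 to +0.014 |
| Lenient, cap of 20 | 19.1 to 20.0 | +0.039 to +0.066 | +0.015 to +0.035 |
| Strict, no cap | 6.0 to 9.6 | +0.080 to +0.168 | +0.035 to +0.076 |

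The Monte Carlo standard error of the test-retest bias is at most 0.006. As an example, with 62 equal items under the lenient rule capped at 20, test-retest is 0.832 on the same data and 0.766 on new data (0.066 too high). Inter-rater is 0.896 against 0.862 (about 0.035 too high).

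The bias is absent without selection and present in every selection setting, so it comes from reusing the selection data.

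**5. Limits of the simulation.** The 12 double-rated residents were generated separately from the 40, although in the plan they are among them. The 5% frequency rule and the factor analysis were not simulated; the cap stands in for further pruning. Under the strict rule, replicates keeping fewer than 3 items were dropped (544 to 598 of 600 remained).

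**The case against.** **Same-sample reliability is a usual first step, and the bias may be smaller than sampling error.** With a Fisher z interval (variance 1/(n − 3/2)), a test-retest ICC of 0.83 on 40 residents has a 95% interval of about 0.70 to 0.91, and 0.77 lies inside it. An inter-rater ICC of 0.90 has about 0.70 to 0.97 on 12 independent pairs, or 0.84 to 0.94 if all 60 paired sessions counted as independent. This stands as a comment on severity. A wide interval does not remove a bias of known direction, and it would be centred on the biased value.

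**Labelling and correction could be left to an analysis plan.** This stands only in part. The article itself fixes the use of one sample for selection and evaluation, and it lists the Stage Three analyses without a reliability estimate.

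**Stronger readings a reader might infer, which the article does not support:**

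- *That the inter-rater step is the most exposed because it has only 12 residents.* For the scale score, the test-retest bias was the larger in every selection setting.
- *That the overstatement is 0.06 to 0.09.* This comes from mean kappa per retained item under assumed cut-offs: 0.725 − 0.667 = 0.058 at 0.6, and 0.789 − 0.702 = 0.087 at 0.7. Analysis (b) concerns the scale, the article states no cut-off, and its wording is compatible with a lenient floor. The pool of 62 is also uncertain, since Stage One may shorten it and Stage Two may add to it.
- *That the user manual will quote the inflated coefficient, or that entry to Stage Three depends on it.* Neither is stated.
- *That the trial result is compromised.* The resident outcomes named in the Abstract are behaviour, well-being and quality of life, not the awareness score.

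**Conclusion.** The concern holds in direction. Analysis (b) as written gives upward-biased test-retest and inter-rater coefficients for the new measure, and the article plans no reliability estimate in new residents.

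The size is unknown. Under the assumed settings the test-retest ICC is too high by about 0.02 to 0.07 with lenient cut-offs and 0.08 to 0.17 with strict ones. The inter-rater ICC is too high by about 0.01 to 0.035 and 0.035 to 0.08. These ranges rest on the assumed cut-offs, item pool and variance components. The bias is smaller when many items survive a mild rule and larger when a strict rule leaves a short scale.

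The consequence is confined to the claim that the measure is reliable. The randomised comparison and the Stage Three sample size are unaffected. The change should be made, but nothing in the trial design turns on it.

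**What to change.** 1. **Label.** Report the Stage Two coefficients as development-sample estimates wherever they appear.
2. **Test-retest (40 residents).** Write down the item-selection rule in advance (reliability cut-offs, the 5% frequency rule, the factor-analytic criterion). Repeat the whole sequence in bootstrap resamples of residents and report the optimism-corrected ICC beside the apparent one. The factor-analytic step must be a stated rule, because case-by-case judgement cannot be repeated in each resample.
3. **Inter-rater (12 residents).** Report the coefficient with a confidence interval clustered by resident. Do not rely on residents left out of bootstrap resamples: on average only 12 × (11/12)^12 = 4.2 are left out, too few for a stable ICC.
4. **New homes.** Add to the Stage Three Data analysis section an inter-rater analysis of the paired staff observations already scheduled in the intervention homes. State that these are 10-minute ratings by staff, possibly not concurrent. They estimate reliability in routine use and do not replicate the 30-minute researcher ratings. The observation schedule need not change for this; altering it would change how the intervention is delivered.

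The cost is a little more analysis, an earlier commitment to a selection rule, and somewhat lower reported reliability. No further participants are needed.
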